### Research Questions

1. Do youth (12 to 17 years of age) who engage in the 6-month HELP e-intervention have a larger improvement in emotional health (measured by the Strengths and Difficulties Questionnaire) than youth who do not receive the intervention?
2. Does engagement in the HELP e-intervention improve lifestyle behaviour (physical activity, sleep or screen time)?
3. Are changes in emotional health and lifestyle behaviours sustained for at least 6 months after completion of the HELP e-intervention?
4. Do youth who engage in the 6-month HELP e-intervention utilize fewer mental healthcare resources, during and for 1 year following RCT participation, than youth who do not receive the intervention?
5. Do mental health professionals supporting youth who engage in the 6-month HELP e-intervention provide lifestyle behaviour support less frequently than for youth who do not receive the intervention?
6. Are self-reported (i.e., perceived) lifestyle behaviour changes (study questionnaire responses) aligned with objective measures of screen time (smartphone tracking) and sleep and physical activity (accelerometry) in a randomly selected sub-sample (1 of 3) enrolled participants?

We hypothesize that youth engaging in the HELP e-intervention will have improved emotional health and enhanced lifestyle behaviours in comparison to those receiving the delayed (post 6-months) intervention. We hypothesize that changes during the intervention will be maintained for an additional 6 months, and that self-reported measures will accurately reflect objective measurements. We hypothesize that youth engaging in the HELP e-intervention will require fewer youth mental health supports, and when supported will be less likely to require treatment directed at lifestyle behaviours.

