### HELP E-Intervention

All study participants will have access to the HELP e-intervention either immediately (HELP access between 0 and 6 months) or after a wait of 6 months (control condition, access between 6 and 12 months). The use of a wait list control is expected to decrease the impact of randomization on study recruitment and retention. Our unique HELP e-resources utilize age-appropriate graphics and interactive formats developed collaboratively with youth/parent/clinician partners. There are 4 sections: 1) Know Your Habits, 2) Physical Activity, 3) Screen Time, 4) Sleep. Know Your Habits provides youth with their personal baseline questionnaire results. Messages are tailored to each youth’s readiness for behaviour change and assessment results. Each behaviour section (physical activity, screen time, sleep) has 4 sub-sections. “Learn” conveys information linking the behaviour and youth mental health and targets youth not yet contemplating behaviour change. “Pros and Cons” targets ambivalence, supporting youth to consider the barriers/facilitators of behaviour change. “Goals” guides youth to choose from >70 step-by-step change plans. Each plan contains a sequence of 6-8 steps that youth complete to achieve their goal. Steps vary in required time (2-30 mins) and youth proceed through the steps at their preferred pace. SMART goal, overcoming road blocks and additional kinesiologist support resources are also provided. Youth can track their goals and accomplishments on the website. Access to all HELP e-modules is available to all youth but the website suggests individualized avenues for change based on each participant’s assessment results. Sample pages from the HELP e-intervention are provided in Appendix H.

Each participant will have a unique login to the HELP e-intervention (found at www.cheoactive.ca). By automatically tracking e-resource use (site visits, interactivity use, knowledge component completion), the website provides data regarding participant engagement with the intervention. These data also assess the frequency or type of e-resource use, important considerations in analyzing the intervention impact on behaviour change. Comparing initial and post-intervention questionnaire responses will indicate the potential emotional health/lifestyle behaviour change impacts of HELP e-resource access.

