Secondary efficacy outcomes are measures of readiness for behaviour change (i.e., stage of change) and sleep, physical activity and screen time behaviour. Behaviour change theory emphasizes that individuals move through a series of stages, with the most effective intervention differing for each stage. HELP supports youth in all stages of change. “Learn” targets youth not yet considering behaviour change. “Pro’s and Con’s” guides youth to address their ambivalence towards change. “Goals” provide step-by-step plans so youth can act on their intention to change behaviour. “Roadblocks” support the maintenance of recent behaviour changes. Paired t-tests will examine participants’ stage of change at enrollment and 6 months to assess whether HELP enhanced their readiness for behaviour change. Modeling how the behaviour change stage differs, with adjustments for age, gender, intervention adherence, type of mental health concern and support referral, will assess whether HELP similarly impacts behaviour change among all youth. The same analyses will be completed for each behaviour outcome with stage of change at 6-months a mandatory variable as theory indicates that achieving Stages 3 to 5 is required for behaviour change to occur (Stages 1 & 2 are moving toward the decision to change behaviour).

A repeated measures model of the primary and secondary outcomes will evaluate changes between study groups, comparing changes occurring during intervention access to changes when the intervention is not available. Changes between the 0 and 6-month assessments for youth randomized to immediate intervention access and between the 6 and 12-month assessments for youth randomized to the wait list group will evaluate HELP e-intervention efficacy. Differences between the 6 and 12-month assessments for youth randomized to immediate intervention access will evaluate the sustainability of the intervention effects. Differences between the 0 and 6-month assessments for youth randomized to the wait list group will evaluate changes in study outcomes over time without the HELP e-intervention. Comparisons between 0 and 3-month and 3 and 6-month outcomes will determine the required length of the HELP e-intervention for optimal outcomes. All models will be adjusted for age, gender, intervention adherence, type of mental health concern and support referral.

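### Six-month stage of change, itself a HELP outcome, is a mandatory variable in the behaviour analyses, so any HELP effect estimated there loses the part acting through stage

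*Protocol*

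**What the plan says.** All of this is in the Protocol, mainly in Statistical Plan, Efficacy Outcomes.

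- **Stage of change is an outcome.** The second paragraph states: "Secondary efficacy outcomes are measures of readiness for behaviour change (i.e., stage of change) and sleep, physical activity and screen time behaviour".
- **HELP is expected to move it.** Paired t-tests compare stage at enrolment and 6 months "to assess whether HELP enhanced their readiness for behaviour change".
- **Stage comes before behaviour.** The reason given for the covariate rule is that "theory indicates that achieving Stages 3 to 5 is required for behaviour change to occur".
- **The rule.** For the three behaviours, "The same analyses will be completed for each behaviour outcome with stage of change at 6-months a mandatory variable".
- **A second analysis of the same outcomes.** The third paragraph describes a repeated measures model that compares the study groups on the primary and secondary outcomes. Its covariates are age, gender, intervention adherence, type of mental health concern and support referral. Stage of change is not among them.
- **The question to be answered.** Research question 2 asks: "Does engagement in the HELP e-intervention improve lifestyle behaviour (physical activity, sleep or screen time".

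The primary SDQ model, in the first paragraph of Efficacy Outcomes, does not list stage of change.

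**The concern.** A covariate that treatment can change, and that in turn changes the outcome, is a mediator. Adjusting for it compares youth in the two groups who ended at the same stage. That comparison leaves out whatever HELP achieved by moving youth to a later stage. It also gives up the protection of randomisation. Youth who reach a given stage with HELP may differ from youth who reach it without HELP, so anything that drives both stage and behaviour can bias the result.

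The protocol's reason for including 6-month stage, that later stages are needed before behaviour changes, is the reason why it should not be adjusted for when the effect of HELP is estimated. Research question 2 asks for the effect of HELP on behaviour, not the effect net of stage. If the stage-adjusted model were read as the answer, a real benefit could be understated or missed. The protocol does not say which of its two behaviour analyses is to be read that way.

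**Working it through.** **1. The protocol's own figures.** Sample Size Determination gives 122 youth with complete data, 80% power and a 3.4-point SDQ difference. Data Analyses sets p<0.05. No SD, sidedness or allocation ratio is stated. Assuming a two-sided test and 61 per arm:

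SD = 3.4 / [(1.960 + 0.842) × √(2/61)] = 3.4 / (2.802 × 0.1811) = 6.70, so d = 3.4 / 6.70 = 0.507.

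The 122 is consistent with an SD of about 6.7 (about 7.55 if one-sided, d = 0.45), but cannot be reproduced independently. The protocol gives no effect, SD or power for any behaviour outcome. Using 0.507 SD for them is an assumption that only sets a scale.

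**2. Effect of adjusting, linear model.** Let τ = 0.507 be the total effect, m the share acting through stage, and a the shift in stage due to HELP (assumed 0.6 SD). Stage and behaviour have within-arm SD 1. The slope of behaviour on stage is b = mτ/a. Then

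- adjusted effect = (1 − m)τ
- standard error = √(1 − b²) × √(2/61) × √(1 + a²/4)

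For m = 0.5: effect = 0.254; b = 0.254/0.6 = 0.4225; SE = 0.906 × 0.1811 × 1.044 = 0.171; ratio = 1.48; power ≈ Φ(1.48 − 1.96) = 0.32. Simulation (6,000 trials per setting) agrees:

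| Share through stage | Unadjusted estimate, power | Adjusted estimate, power |
| --- | --- | --- |
| 0% | 0.51, 79% | 0.51, 75% |
| 25% | 0.51, 79% | 0.38, 53% |
| 50% | 0.51, 79% | 0.25, 31% |
| 75% | 0.51, 79% | 0.13, 14% |
| 100% | 0.51, 80% | 0.00, 5% |

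With a = 0.8 instead, m = 0.5 gives b = 0.317, SE = 0.948 × 0.1811 × 1.077 = 0.185, ratio 1.37 and power Φ(−0.59) = 0.28. So the result at half mediation is about 30% under either shift.

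**3. Shared cause of stage and behaviour.** Suppose an unmeasured factor loads 0.4 on each and there is no mediation at all. The slope on stage within arm is 0.4 × 0.4 = 0.16, so the adjusted effect is 0.507 − 0.6 × 0.16 = 0.411. Simulation gave 0.41 SD with 59% power. The estimate is biased although nothing runs through stage.

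**4. Threshold version of the protocol's theory.** Suppose behaviour responds only in Stages 3 to 5, and 70% v 30% reach them (assumed).

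- No other pathway: the total effect is 1.27 × (0.7 − 0.3) = 0.51. The adjusted estimate was 0.00.
- HELP also adds 0.36 SD among youth in those stages: the total is (0.64 + 0.36) × 0.7 − 0.64 × 0.3 = 0.51. In simulation the estimate fell from 0.50 to 0.17 SD.

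**5. Timing.** HELP E-Intervention gives access "either immediately (HELP access between 0 and 6 months) or after a wait of 6 months (control condition, access between 6 and 12 months". Six-month stage is therefore measured after HELP in one arm and before HELP in the other. If the rule were carried into an analysis that combines access periods across arms, as the third paragraph of Efficacy Outcomes describes, one covariate would be a mediator in one arm and a baseline value in the other.

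**The case against.** The strongest reply is that the protocol has another analysis. The between-group repeated measures model in the third paragraph covers the same outcomes, is described as the evaluation of efficacy, and does not list stage. The paragraph with the stage rule describes paired t-tests and a model that "will assess whether HELP similarly impacts behaviour change among all youth", with no study-group term spelled out. On that reading, stage enters an explanatory analysis of who changes.

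This narrows the point but does not remove it. The rule is stated without an exploratory label, it applies to efficacy outcomes, and no order between the two analyses is given. The between-group model is not a clean fallback either. It adjusts for intervention adherence, which is also determined after randomisation, and the wait-list group has nothing to adhere to in months 0 to 6.

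A reader might infer that the rule wipes out the HELP effect, so that research question 2 would be answered no precisely when HELP works as designed. The document does not support that. Reaching Stages 3 to 5 is described as necessary for change, not as the only route by which HELP acts. The same paragraph says that HELP supports youth in every stage, with components for acting on an intention and for maintaining change. Working as designed therefore includes effects within Stages 3 to 5, and those are not all lost (0.17 of 0.50 SD in the second threshold case).

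A reader might also infer that the plan cannot test whether HELP works similarly in all youth because no interaction is named. That is a separate and weaker matter: no model equation is given, and interaction terms may be left to a statistical analysis plan.

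**Conclusion.** The point holds in a limited form. The protocol fixes a post-randomisation mediator as a mandatory variable for sleep, physical activity and screen time. Any HELP effect estimated from that model loses the part acting through stage, and all of it only under full mediation. Shared causes of stage and behaviour can add bias.

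The loss of the mediated part does not depend on the assumed numbers; its amount does. About 0.25 SD and about 30% power at half mediation rests on a borrowed total effect of 0.51 SD, 61 per arm, a two-sided test, a linear model and an assumed stage shift of 0.6 to 0.8 SD. None of these is a protocol figure for the behaviours.

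The problem affects secondary outcomes, in one of two described analyses. Together the two paragraphs give different covariate rules for the same outcomes with no stated precedence. The primary SDQ model is not affected by the stage rule, although it does list adherence.

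**What to change.** In Efficacy Outcomes:

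1. Remove 6-month stage of change from the models that estimate the effect of HELP on sleep, physical activity and screen time. If adjustment for stage is wanted, use stage at enrolment.
2. State that the between-group repeated measures model, without 6-month stage, answers research question 2.
3. Keep 6-month stage as a secondary outcome in its own right, or in a mediation analysis labelled exploratory, with its assumption of no unmeasured shared causes stated.
4. Treat intervention adherence in the same way: take it out of the models for the randomised comparison and report it in a separate, labelled analysis. Without this step the between-group comparison is still not protected by randomisation.

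The cost is wording only. Study Assessments has every participant complete all questionnaires, including stage of change, at month 0, so no new data, visits or participants are needed.

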# Statistical Plan

## Sample Size Determination

The size of the study sample will be determined by the number of eligible youth contacts (with 1Call1Click or directly to the research team). Our pilot study approached 5-10 youth/week via 1Call1Click with 25% enrolling, providing an expected 400-800 potential and ~100-200 enrolled participants over 18 recruitment months. Complete data for 122 youth would provide 80% power to detect a 3.4 point difference in emotional health (Strengths & Difficulties Questionnaire), equivalent to the 19.5% improvement observed in our 3-month pilot study.

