## Data Analyses

Data cleaning will be on-going throughout data collection. Initial data analyses of youth enrolled in the first 9 months of the RCT will be completed in months 15-20. Detailed analysis syntax and modeling will be retained for use in the final modeling/analyses when data collection is complete. Statistical significance will be set at p<0.05 for all analyses.

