### Efficacy Outcomes

The primary outcome is youth emotional well-being as measured by the Strengths & Difficulties Questionnaire (SDQ^34^). We define a clinically significant improvement as a score decrease of 15%, with the reduction occurring only when participants have engaged with the intervention. This change is just less than 1/2 of the SDQ improvement observed after 6 months of specialist community mental health services^43^. We do not expect HELP benefits to be equivalent to traditional mental health interventions. However, we believe that the ability to improve emotional health half as well as traditional therapies would provide a meaningful and important change. In our pilot study, SDQ scores improved by 19.5% in 3 months among engaged youth. We will evaluate the change in SDQ from baseline to 6 months in a repeated measures model adjusted for age (years), gender, intervention adherence, type of mental health concern (e.g., anxiety, depression, etc. as documented during 1Call1Click intake), and support referral (community or specialist services recommended by 1Call1Click intake staff). The impact of sex will be investigated if participants include a sufficient number of youth who do not identify as the gender aligned with their sex.

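### The efficacy section mixes the randomised 0-6 month between-arm contrast with non-randomised within-person changes and does not fix which one is the efficacy estimate

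*Protocol*

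**What the plan says.** Study Objectives and Study Design describe a randomised comparison of immediate access with access delayed by 6 months. For the primary outcome, Efficacy Outcomes states: "We will evaluate the change in SDQ from baseline to 6 months". This is to be done in a repeated measures model with covariates; the sentence names neither study group nor a group-by-time term.

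The same section then makes four further statements.

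- A repeated measures model of primary and secondary outcomes looks at change between the study groups, "comparing changes occurring during intervention access to changes when the intervention is not available".
- The immediate arm's 0-6 month change "and between the 6 and 12-month assessments for youth randomized to the wait list group will evaluate HELP e-intervention efficacy". The immediate arm's 6-12 month change is assigned to sustainability. The wait-list arm's 0-6 month change is assigned to describing change over time without HELP.
- Paired t-tests examine "stage of change at enrollment and 6 months to assess whether HELP enhanced their readiness for behaviour change". The next sentences add an adjusted model and extend the same analyses to each behaviour outcome.
- Comparisons of 0-3 with 3-6 months "will determine the required length of the HELP e-intervention for optimal outcomes".

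The schedule table under Expected Duration of Participation shows that the wait-list arm has HELP in months 6-12, after the immediate arm's access has ended.

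**The concern.** Randomisation protects one comparison: immediate against delayed access over months 0-6. After month 6 every participant has had HELP or has access to it, so the wait-list arm's later change has no concurrent untreated arm. A before-after test within participants has none at any time.

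The protocol itself gives reasons to expect scores to move without HELP. Youth enrol while seeking, waiting for or receiving support (Inclusion Criteria), and other mental health care is unrestricted (Study Assessments). Efficacy Outcomes puts SDQ improvement after 6 months of specialist services at a little more than twice 15%. Natural recovery, regression to the mean and other care could therefore be credited to HELP or subtracted from it.

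Because two kinds of contrast both carry the efficacy label, the conclusion could also depend on which is reported. The length sentence has a separate problem: nobody is randomised to stop at 3 months, so the data cannot show what a shorter programme would have achieved.

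**Working it through.** **Inputs from the protocol.** Sample Size Determination: "Complete data for 122 youth would provide 80% power to detect a 3.4 point difference in emotional health", and the 3.4 points are "equivalent to the 19.5% improvement observed in our 3-month pilot study". The implied baseline is 3.4/0.195 = 17.4 points, so 10% is 1.74 points, 15% is 2.6 and 30% is 5.2. Data Analyses: "Statistical significance will be set at p<0.05 for all analyses".

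**Assumptions.** The SD, allocation ratio, sidedness, natural trend and fading are not given. I take 1:1 allocation and two-sided testing, and vary the rest.

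**The plan's own figure.** 122 cannot be reproduced independently without an SD. Solving for the SD with 61 per arm:

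SD = 3.4 × √(61/2) / (1.96 + 0.84) ≈ 6.7.

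So 122 fits a two-arm contrast if the SD is about 6.7. At SD 5, 6, 7 and 8 the total would be 68, 98, 134 and 174.

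**Notation** (improvement positive). E is the HELP effect; T1 and T2 are natural change in months 0-6 and 6-12; L is the benefit lost after access ends. Expected changes:

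| Arm | 0-6 months | 6-12 months |
|---|---|---|
| Immediate | T1 + E | T2 − L |
| Wait list | T1 | T2 + E |

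**Randomised contrast, 0-6 months.** (T1 + E) − T1 = E. Neither trend nor carry-over enters.

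**Reading A: off-access time is wait-list 0-6 months only**, following the section's own label of the immediate arm's 6-12 months as sustainability.

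[(T1 + E) + (T2 + E)]/2 − T1 = E + (T2 − T1)/2.

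The bias is half the difference in natural change between the periods.

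- Equal trends: zero.
- T1 = 1.74, T2 = 0: −1.74/2 = −0.87 points, which is 0.87/3.4 = 26% of the planned difference and understates HELP.
- T1 = 2.6, T2 = 0: −1.3 points.
- T1 = 0, T2 = 1.74: +0.87 points.

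**Reading B: all off-access time counts, with balanced numbers.**

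[(T1 + E) + (T2 + E)]/2 − [T1 + (T2 − L)]/2 = E + L/2.

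Common trends cancel; carry-over does not. With E = 3.4:

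- half the benefit fades (L = 1.7): 4.25, overstated by 25%;
- all fades (L = 3.4): 5.1, overstated by 50%;
- improvement continues by 1.7 (L = −1.7): 2.55, understated by 25%.

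If numbers are unequal in months 6-12 (assumed 55 and 43 remaining), a 2.6-point trend confined to months 0-6 leaves a residual of 0.16 points.

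**Paired t-test, enrolment versus 6 months.** In treated youth the expectation is T1 + E, so the trend enters in full. Rejection probabilities with E = 0, from the noncentral t distribution at two-sided 0.05:

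| Assumed trend, in SDs of change | 61 youth | 122 youth |
|---|---|---|
| 0.15 | 21% | 37% |
| 0.26 | 52% | 81% |
| 0.39 | 85% | 99% |

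These trends correspond to 1.0, 1.74 and 2.6 points on an SD of 6.7. They borrow the SDQ scale, whereas the paired tests are planned for stage of change and behaviours, for which the protocol gives no trend or SD. The table is an illustration only. If the tests take in both arms, youth who have not yet had access are counted as evidence about HELP.

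**Length.** Both assessments, at 3 and 6 months, fall within continuous 6-month access in the immediate arm. They describe the course under continued access, not the result of stopping earlier.

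**The case against.** A reader might infer that the protocol replaces the randomised comparison with within-person change. The text does not support that. The objective, the first research question and the design all compare immediate with delayed access. The primary-outcome sentence uses the 0-6 month window. The modelling sentence itself refers to change between study groups, and the stated sample size is compatible with a two-arm contrast. The randomised contrast is mixed with other changes, not displaced.

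Three further points on that side stand.

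- The section does not say that the on-access periods are averaged into one estimate. It gives each arm and period a role, so Readings A and B are constructions that the wording permits.
- Time trend does not bias every version. It cancels in Reading B when numbers are balanced, and in Reading A it vanishes when trends are equal.
- The paired tests are not planned for the SDQ, and they are not the only analysis of the secondary outcomes, because the repeated measures model covers those too.

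It is also fair that period terms and the exact model specification may sit in a statistical analysis plan that is not shown; I do not count their absence. What remains is what the protocol does state: an uncontrolled wait-list change labelled efficacy, uncontrolled paired tests said to show whether HELP worked, and a length claim that the design cannot support.

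**Conclusion.** The point holds as an unresolved mixture. The protocol does not fix the randomised 0-6 month between-arm difference as the efficacy estimate, and it gives the same standing to changes that randomisation does not protect.

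The size and even the direction of the bias depend on the reading and on assumed trends. Reading A gives nothing under equal trends and -0.87 points under an assumed 10% improvement confined to months 0-6. Reading B gives an overstatement of 25% to 50% if half to all of the benefit fades. The paired tests are the most exposed, because any trend enters in full; the 52% and 81% rejection rates rest on an assumed 0.26 SD trend and are illustrative. The length claim fails by design, whatever the numbers.

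**What to change.** In Efficacy Outcomes:

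1. Name the between-arm difference over months 0-6, as randomised, as the efficacy analysis for the primary and secondary outcomes.
2. Replace the paired t-tests with the between-arm difference at 6 months adjusted for the baseline value, for stage of change and for each behaviour.
3. Label the wait-list arm's 6-12 month change (replication) and the immediate arm's 6-12 month change (maintenance) as uncontrolled supportive descriptions.
4. Reword the length sentence so that it describes the between-arm difference at 3 and at 6 months.

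The cost is wording in the protocol and any analysis plan. No new data are needed, and 122 complete participants already fit a two-arm contrast if the SD is about 6.7. The downside is that the wait-list arm's 6-12 month data no longer contribute to the main efficacy estimate.

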# Study Design

This research will investigate the patient and healthcare system impacts of the HEalthy Lifestyle Project (HELP) e-intervention. The research design is a randomized, controlled trial comparing youth who immediately receive the intervention to youth randomized to receive the intervention 6-months later (wait list control). Efficacy outcomes will be assessed at 0, 3, 6 and 12 months. Healthcare system impacts will be extracted from medical records from 0 to 18 months.

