## Expected Duration of Participation

Youth will participate in the study for 12 months. All study visits and assessments are completed remotely. Youth can choose to complete the assessments via RedCAP survey or to have paper copies of the questionnaires sent by mail. The research coordinator will work virtually with each participant to support questionnaire completion. Completion of all questionnaires will require approximately 1 hour at each assessment timepoint. One of every three participants will be randomly selected to complete the objective behaviour measurements in addition to the questionnaires. Accelerometers will be distributed and collected by mail so that in-person visits to CHEO are not required. Participants selected for the objective measures will be required to wear an accelerometer on an elastic waistband 24 hours per day for 7 consecutive days. They will also be required to submit a screen shot of their social media screen time (app that already exists in smartphones) daily for the same 7 days. After the four assessment timepoints have been completed, youth will no longer be required to perform study activities but data collection on healthcare system impacts will continue to be collected via medical chart review for an additional 6 months. Participants randomized to the wait list control group will have access to the HELP e-intervention between the 6 and 12-month assessment timepoints.

| **Study Group** | **0 mos** | **0 to 3 mos** | **3 mos** | **3 to 6 mos** | **6 mos** | **6 to 12 mos** | **12 mos** | **12 to 18 mos** |
| --- | --- | --- | --- | --- | --- | --- | --- | --- |
| Intervention | Assess | HELP | Assess | HELP | Assess | ----- | Assess | Medical chart |
| Wait List Control | Assess | ----- | Assess | ----- | Assess | HELP | Assess | Medical chart |

Assess = completion of study questionnaires and objective measures (if applicable)
HELP = access to the HELP e-intervention with kinesiologist support
Medical chart = evaluation of mental health service use and inclusion of lifestyle behaviours in mental health service supports via medical chart review for 18 months from study enrollment

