In our pilot study, youth who engaged with the HELP e-intervention demonstrated positive changes to emotional well-being and lifestyle behaviours. However, initiating routine engagement with the intervention was a struggle for a majority of participants. To facilitate their engagement into the study, the research coordinator will directly engage with enrolled youth 2-3 times/week until they are independently able to implement the intervention. Regular contacts with the research coordinator (via telephone, zoom or Facetime as per participant preference, Appendix I) throughout the 6-month intervention will support youth to engage with the intervention activities. The extent of this support provided to each participant will be tracked (# of sessions, length and content of each session).

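### The comparison of months 0-3 with months 3-6 cannot determine the required length of HELP, because every participant is given the same 6-month access

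*Protocol*

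**What the plan says.** The last analysis described under Efficacy Outcomes carries a firm conclusion: "Comparisons between 0 and 3-month and 3 and 6-month outcomes will determine the required length of the HELP e-intervention for optimal outcomes". The wording is that the comparison will settle the matter, not explore or describe it. The sentence does not name the groups being compared.

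The design around it is as follows.

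- **Arms.** Study Design describes two randomised groups, one starting HELP at once and one starting six months later. There is no arm defined by course length.
- **Length of access.** HELP E-Intervention gives the immediate group months 0 to 6. Expected Duration of Participation gives the other group the same length later: "Participants randomized to the wait list control group will have access to the HELP e-intervention between the 6 and 12-month assessment timepoints".
- **Support.** Regular contacts with the research coordinator "throughout the 6-month intervention will support youth to engage with the intervention activities". No planned stop at month 3 appears anywhere.
- **Assessments.** "Efficacy outcomes will be assessed at 0, 3, 6 and 12 months". The wait-list group is therefore not assessed midway through its own course.
- **After access ends.** "Differences between the 6 and 12-month assessments for youth randomized to immediate intervention access will evaluate the sustainability of the intervention effects". Post-access outcomes are seen only after a full six-month course.

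**The concern.** To say what length is required, one must know what would happen under other lengths. At the least that means the outcome for a youth whose access ends at month 3, and ideally the outcome for one who continues past month 6. Neither is observed here. The 0-3 and 3-6 month periods are two halves of one six-month course, not two courses.

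The unnamed groups add a second problem. If the comparison is made within the HELP arm alone, change over each period includes whatever would have happened without HELP, including regression to the mean in youth who enrol while in distress.

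What is at stake is an implementation decision. The pilot ran for 3 months and supplied the 19.5% improvement behind the sample size, so a reader could easily take a flat second half to mean that three months is enough. The trial would not have tested that.

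**Working it through.** **The plan's own figure.** The only power statement is "Complete data for 122 youth would provide 80% power to detect a 3.4 point difference in emotional health". No SD is given, so 122 cannot be reproduced independently. Solving backwards, with 61 per arm, two-sided alpha 0.05 and 80% power (allocation ratio and sidedness are assumptions):

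SD = 3.4 / [(1.96 + 0.842) × √(2/61)] = 3.4 / 0.507 = 6.70.

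At SDs of 6, 7 and 8 the total would be 98, 134 and 174. The identification argument below does not depend on any of these.

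**Is required length identified?** A drop of 3.4 points equal to 19.5% implies a baseline of 3.4 / 0.195 = 17.4. Suppose the HELP arm shows means of 17.4, 14.0 and 14.0 at 0, 3 and 6 months, and, for simplicity, the wait-list arm stays at 17.4.

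| | Scenario A: benefit persists if access ends at month 3 | Scenario B: benefit is lost if access ends at month 3 |
| --- | --- | --- |
| Observed HELP means (0, 3, 6 months) | 17.4, 14.0, 14.0 | 17.4, 14.0, 14.0 |
| Within-arm improvement, 0-3 and 3-6 | 3.4 and 0 | 3.4 and 0 |
| Between-arm difference at 3 and 6 months | 3.4 and 3.4 | 3.4 and 3.4 |
| Unobserved: 6-month mean after a 3-month course | 14.0 | 17.4 |
| Value of months 3-6 of access | 14.0 − 14.0 = 0 | 17.4 − 14.0 = 3.4 |

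Every observed quantity is the same, yet in A the second half adds nothing and in B it carries the whole benefit. This holds for the within-arm and the between-arm comparison alike, and at any sample size. Access beyond six months is unobserved in the same way.

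**Does it matter which groups are compared?** For the time course, yes. As an illustration only, let HELP truly add 1.7 points in each half (3.4 in total), and let untreated youth improve by 1.0 to 2.0 points in one half and 0.2 to 0.5 in the other. These natural changes are assumed; the protocol gives none.

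- Between arms, natural change cancels in expectation: first-half share = 1.7 / 3.4 = 50%.
- Within the HELP arm, larger natural change first: halves of 2.7 to 3.7 and 1.9 to 2.2. The share runs from 2.7 / (2.7 + 2.2) = 55% to 3.7 / (3.7 + 1.9) = 66%.
- Within the HELP arm, larger natural change second: the share runs from 1.9 / (1.9 + 3.7) = 34% to 2.2 / (2.2 + 2.7) = 45%.

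The within-arm figure can be off in either direction.

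**How precisely can the time course be described?** With 61 per arm and SD 6.7, the 95% CI half-width for the between-arm difference in 3-to-6-month change is 1.96 × 6.7 × √[2(1 − r)] × √(2/61). For an assumed correlation r of 0.5 this is 2.4 points; for 0.7 it is 1.8 points. A second-half gain of 1.7 points could not reliably be told from none.

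**The case against.** The strongest case against the point is that the sentence sits in a paragraph that opens with a repeated measures model of changes between the study groups, and that both arms are assessed at 0, 3 and 6 months. Read that way, the comparison is randomised. The 3-month contrast validly estimates the effect of three months of access measured at month 3, and the two contrasts together can show whether benefit levels off. That stands, and it limits the criticism. It does not rescue the claim about required length, since the table gives the same answer for the between-arm reading.

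It is also fair that course length is not among the six Research Questions, is not a listed outcome and plays no part in the sample size. Website tracking of use does not fill the gap, because youth choose how much to use the site. Nor does the 6-to-12-month follow-up of the immediate arm, since it shows persistence after six months of access, not after three.

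Two stronger readings are tempting, and the protocol supports neither.

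- A reader might infer that the comparison is biased towards a shorter course. That needs a within-arm comparison, which the text does not fix, and natural change concentrated in the first three months, which it does not document. HELP E-Intervention reports that most pilot participants found it hard to start engaging and lets youth set their own pace, which could equally push benefit later.
- A reader might treat the coordinator contact two or three times a week at the start as a confounder. Study Objectives and the schedule legend define the intervention as HELP access with kinesiologist support, and HELP E-Intervention describes these contacts as part of its delivery. They belong to the package under test. They also last until the youth can work independently, not for a fixed three months.

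**Conclusion.** The point holds in this form: the protocol promises a conclusion about required length that its design cannot yield. This follows from the equal six-month access in both arms and needs no numerical assumption. In the worked example, the unidentified part ranges from 0 to 3.4 points, the full effect the trial is sized for.

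The unspecified comparison is a lesser fault. Read within the HELP arm, it mixes natural change with the HELP effect; the 34% to 66% range is an illustration that rests on assumed natural changes and applies to that reading alone. Read between arms, the problem disappears in expectation.

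This concerns a secondary conclusion. The primary 0-6 month comparison is unaffected. A statistical analysis plan could name the groups but could not supply the missing course lengths.

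**What to change.** Replace the sentence with: *The randomised between-arm differences in SDQ at 3 months and at 6 months, with 95% CIs, will describe the time course of the effect under 6-month access; a shorter or longer course is not tested.*

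Both arms already complete the SDQ at these visits, so no participant, visit or instrument is added. The contrasts come from a repeated measures model of the kind already planned. They should be taken without the adherence term, because adherence arises after randomisation and conditioning on it would lose the protection the new wording relies on. The only cost is giving up a claim the data cannot support.

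Testing course length itself would need randomisation to different lengths. At the back-solved SD of 6.7, 80% power and two-sided 0.05, that takes 2 × (2.802 × 6.7 / 1.7)² = 244 per group to detect a 1.7-point difference, or 488 in all, against the roughly 100 to 200 enrolments expected under Sample Size Determination. Even a difference of the full 3.4 points would need 61 per group. Rewording is therefore the practical course for this trial.
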